#### Sample Transport and Biobanking

All samples will be collected or delivered to the Hospital del Mar facilities and subsequently processed, analyzed, and stored at the Parc de Recerca Biomèdica de Barcelona (PRBB) facilities and the Cryopreservation Service at the HMRI. Plasma, urine, and saliva will be initially stored at −20 °C and transferred to −80 °C for long-term storage. Hair and nail samples will be stored at room temperature in a locked cabinet under humidity-controlled conditions until processing.

#### Sample Processing Protocols

The collected biological samples will be processed according to standardized protocols prior to laboratory analysis, as outlined below:

Plasma, urine, and saliva: All samples will be centrifuged upon arrival at the laboratory. Aliquots will be prepared as necessary. Chemical treatment will be applied if specified in the manufacturer’s protocol for the collection device (eg, Salivette for saliva). All reprocessing procedures will follow the manufacturer’s instructions.Fingernail samples will be washed with an organic solvent to remove external contaminants, then dried and mechanically ground using a ball mill to produce a homogeneous powder suitable for downstream analysis.Hair samples will undergo solvent-based washing to remove surface contamination, followed by drying and mechanical pulverization using a ball mill to prepare for analytical procedures.

#### Laboratory Oversight and Quality Control

All biochemical analyses will be performed internally in collaboration with the Applied Metabolomics Research Group (LIMA) at the HMRI. Quality control (QC) procedures will include pooled QC samples from healthy donors. At least 3 QC aliquots will be analyzed with each analytical batch.

#### Analytical Methods

The quantification of targeted metabolites in the tryptophan and steroid hormone pathways will be conducted using liquid chromatography-tandem mass spectrometry (LC-MS/MS) across all available biological matrices. This includes the measurement of tryptophan, kynurenine, serotonin, kynurenic acid, and relevant metabolic ratios (eg, kynurenine or tryptophan), as well as estradiol, testosterone, progesterone, cortisol, and their derivatives (eg, 20α-DHE, 20β-DHE). Data acquisition and processing will be performed using MassLynx 4.2 (version 4.2; Waters Corp.) and the TargetLynx application manager (Waters Corp.). To minimize interbatch variability, all samples will be analyzed in a single run once collection is complete. Given the sample size, biomarker analyses will be considered exploratory and hypothesis-generating, and the study is not powered to detect definitive associations.

#### Adverse Events

Participant safety will be monitored throughout the trial. Therapists will assess symptom worsening and psychological distress during individual sessions, with all events recorded in the trial log, and evaluated by the principal investigator or a designated clinician for seriousness, expectedness, and relatedness to the intervention. Per International Council for Harmonisation (ICH) guidelines [32], serious adverse events (SAEs) are defined as any untoward medical occurrence resulting in death, life-threatening outcomes, hospitalization, significant disability, or other medically important conditions.

In this trial, psychological SAEs include suicide attempts, imminent suicidal or homicidal intent, self-harm requiring medical treatment, psychiatric hospitalization, or severe mental state deterioration causing significant impairment. These criteria apply to all events occurring during or after participation, regardless of causality.

SAEs will be reported to the principal investigator within 24 hours and to the research ethics committee as required. Significant safety concerns will trigger a clinical review to determine the need for safety plans, urgent referral, or trial discontinuation. Imminent suicide risk will immediately activate local suicide-risk protocols, including same-day clinical assessment and emergency or crisis service referral.

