### Intervention

#### Experimental Group

Participants in the experimental group will receive the 3D Program—a gender-sensitive, guided iCBT intervention for women with depressive symptoms—delivered over 10 weeks alongside treatment as usual (TAU).

The 3D Program comprises 10 weekly self-guided modules, accessed via a secure website, incorporating video content, written materials, and interactive activities such as worksheets. Topics cover issues commonly experienced by women, including hormonal changes, caregiving, body image, and experiences of sexism. Prior to beginning the program, participants will receive an orientation video on how to navigate the platform.

In addition to the self-guided modules, participants will receive 6 individual online sessions with a trained female psychologist. The intervention adopts a personalized approach, allowing therapists to tailor each participant’s module sequence based on individual needs and clinical relevance. All therapists will complete training focused on the 3D Program and the principles of online psychological support.

Participants will also have access to an online peer support group, moderated by a trained female facilitator who will guide discussions to foster connection and safety. The group aims to reduce isolation, promote shared experiences, and challenge maladaptive beliefs such as “this only happens to me.”

The module content and group space were cocreated and coadapted through 5 workshop sessions with women with lived experience of depressive symptoms. Details on the content of the 3D Program modules are presented in Table S1 in Multimedia Appendix 1.

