#### Control Group

Participants in the control group will receive 6 short informational video capsules based on selected content from the 3D Program modules in addition to TAU. Details on the content can be found in Table S2 in Multimedia Appendix 1.

To ensure an even distribution of content over the 10-week period, participants will be given access to 1 video every 14 days, facilitating regular engagement and structured exposure to the material. Control group participants will not receive interactive tasks or one-to-one sessions with a therapist.

All participants, regardless of group allocation, will continue their TAU under the supervision of their clinical care team. TAU comprises standard Spanish National Health System care, involving primary care coordination and specialist referrals to mental health services as needed. This encompasses psychoeducation, symptom monitoring, and first-line pharmacotherapy with selective serotonin reuptake inhibitors, plus short-term benzodiazepines if needed. Brief psychological interventions (eg, CBT) or more intensive psychotherapy may be provided for mild-moderate cases if indicated [12]. However, individuals currently receiving any such active treatment will be excluded from this trial to avoid potential confounding effects. No modifications to ongoing clinical care will be made for research purposes, ensuring that the 3D Program serves as a naturalistic adjunct to standard treatment.

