#### Relevant Concomitant Care Permitted or Prohibited During the Trial

Pharmacological treatment will be permitted, provided it was initiated at least 1 month before study entry. Concomitant pharmacotherapy (agent and dose) will be recorded at baseline, tracked for changes during subsequent assessments, and compared between the groups after randomization to detect any imbalances. Any concurrent psychological interventions or psychological care will not be permitted during the trial period to avoid confounding effects. Should any intensification of clinical care become necessary during the trial—including psychological interventions, changes to pharmacotherapy, specialist referrals, or crisis interventions—it will be documented in the trial log as part of the adverse event monitoring procedure. Where these intensifications reflect clinically significant symptoms worsening requiring alternate or intensive care, the participant may be discontinued from the trial in consultation with their treating team (see the *Criteria for Discontinuing or Modifying Allocated Interventions* section).

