#### Blinding

This is a single-blind trial. Due to the nature of the intervention, participants will be aware of their group assignment after randomization. Likewise, therapists delivering the intervention will not be blinded, as is standard in psychological trials. To preserve blinding where possible and minimize bias, the following measures will be implemented: (1) outcome assessors will remain blinded to group allocation and will not have access to REDCap fields containing the randomization result; (2) data analysts will be blinded during analyses; and (3) all other stakeholders, including clinicians, statisticians, laboratory analysts, and the principal investigator, will not have access to group assignment information or the randomization sequence. Access control within REDCap will be configured using role-based permissions to ensure that only designated unblinded personnel can view or export the group allocation information.

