#### Procedure

Assessments will be conducted at 3 time points: baseline (T0), postintervention (12 weeks after baseline, T1), and follow-up (26 weeks after baseline, T2).

The baseline assessment will include the collection of sociodemographic and clinical data, the administration of primary and secondary outcome measures, a gynecological consultation to assess hormonal and menstrual health, and the collection of biological samples.

At T1 and T2, follow-up assessments will include the administration of primary and secondary outcome measures as well as biological sample collection.

All psychological assessments will be carried out by a trained professional (psychologist, physician, psychiatrist, or psychiatric nurse), gynecological examinations will be performed by a licensed gynecologist (MD in obstetrics and gynecology), and biological samples will be collected by a registered nurse. Participant timeline, including the schedule of enrollment, interventions, and assessments, is outlined in Table 1. All professionals with direct participant contact—whether via teleconference or in-person—will be women. This decision was reached by consensus within the focus group of women with a lived experience of depression, who expressed that sensitive topics (eg, hormonal changes, gender discrimination, and sexuality in the context of depression) would be better understood by female professionals and that participants would feel more comfortable accordingly.

**Table 1. T1:** SPIRIT (Standard Protocol Items: Recommendations for Interventional Trials) participant timeline.

Study procedure	Trial period					
	Preintervention			Intervention	Postintervention	Follow-up
Time point	–t0	T0	T0	—^a^	T1	T2
Weeks	0	1	2	3‐12	12	26
Enrollment						
Eligibility screen	*✓*					
Informed consent		✓				
Inclusion		✓				
Randomization		✓				
Interventions						
Intervention (3D Program)				✓		
Control group (informational videos)				✓		
Screening assessments						
Sociodemographic information		✓				
Medical and psychiatric history		✓				
Gynecological visit			✓			
Primary outcome						
HDRS-17^b^		✓			✓	✓
Secondary outcomes						
WHODAS 2.0^c^		✓			✓	✓
EQ-5D-5L^d^		✓			✓	✓
PSS^e^** **		✓			✓	✓
MEDI-Q^f^** **		✓			✓	✓
Biological samples						
Plasma			✓		✓	✓
Saliva			✓		✓	✓
Urine			✓		✓	✓
Nails			✓		✓	✓
Hair			✓		✓	✓

a Not applicable.

b HDRS-17: 17-item Hamilton Depression Rating Scale.

c WHODAS 2.0: World Health Organization Disability Assessment Schedule 2.0 (36-item version).

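### Adverse events are actively sought only in therapist sessions that controls do not have, so logged non-serious events are not comparable between arms, and the rule on who judges relatedness conflicts with the blinding statement

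*Protocol article*

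**What the plan says.** All references are to the protocol article.

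- **How events are found.** Under Adverse Events: "Therapists will assess symptom worsening and psychological distress during individual sessions, with all events recorded in the trial log". No other active enquiry is described.
- **Who has such sessions.** Under Experimental Group, "participants will receive 6 individual online sessions with a trained female psychologist"; the section on improving adherence gives this as up to 6. Under Control Group, "Control group participants will not receive interactive tasks or one-to-one sessions with a therapist".
- **What the shared visits contain.** Under Procedure, "At T1 and T2, follow-up assessments will include the administration of primary and secondary outcome measures as well as biological sample collection". Table 1 has no adverse-event row.
- **A route open to both arms.** The section on concomitant care covers any intensification of care during the trial and says that "it will be documented in the trial log as part of the adverse event monitoring procedure".
- **Who judges events.** Under Adverse Events, they are to be "evaluated by the principal investigator or a designated clinician for seriousness, expectedness, and relatedness to the intervention".
- **Who is blinded.** Under Blinding, "therapists delivering the intervention will not be blinded, as is standard in psychological trials", while all other stakeholders, "including clinicians, statisticians, laboratory analysts, and the principal investigator, will not have access to group assignment information or the randomization sequence".

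**The concern.** There are two linked problems.

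First, the chance that an event enters the log depends on the arm. A woman on the 3D Program is asked about worsening and distress by a therapist on several occasions during treatment. A control participant is not asked by anyone in the trial, as far as the article says. Her event is logged only if something else brings it to notice. A table of logged events by arm would then mix true differences with differences in how hard the trial looked. The distortion runs against the program.

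Second, the person who judges relatedness is declared blinded but receives reports that can disclose the arm. Only one arm has therapist sessions, so a report from a session identifies an experimental participant. Adverse Events and Blinding cannot both hold as worded.

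At stake are the fairness of the safety report and the accuracy of the blinding statement. There is no independent data monitoring committee, so the team's own monthly safety review relies on what has been recorded.

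**Working it through.** **Ascertainment: trial contacts with a described adverse-event enquiry**

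| Contact | Experimental | Control |
|---|---|---|
| Individual therapist sessions | up to 6 | 0 |
| T1 (week 12) | none listed | none listed |
| T2 (week 26) | none listed | none listed |
| Logging of intensified care | passive | passive |

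The active contacts are up to 6 against 0. All of them belong to the 10-week program, so the imbalance lies in the treatment period. After that, no active enquiry is described for either arm.

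**Arm size.** The plan's own figure reproduces and is not disputed; it only supplies the 60 per arm used below.

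- Inputs from Sample Size Calculation: f = 0.15, α = 0.05, 3 measurements, correlation 0.5, ε = 1, 2 groups.
- Noncentrality = f² × N × m / (1 − ρ) = 0.0225 × 96 × 3 / 0.5 = 12.96, with 2 and 188 degrees of freedom. Power is 0.902, against the stated 0.90.
- Attrition: 96 / (1 − 0.20) = 120, or 60 per arm.

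**Illustration of unequal detection.** The true event rate p and the detection probabilities s are assumptions; none is in the documents. With the same p in both arms:

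- expected logged events per arm = 60 × p × s
- expected ratio = (p × s_exp) / (p × s_ctl) = s_exp / s_ctl, which does not depend on p

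Taking s_exp = 0.90:

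| s_ctl | Ratio | Logged events, p = 10% | Logged events, p = 20% |
|---|---|---|---|
| 0.90 | 1.0 | 5.4 vs 5.4 | 10.8 vs 10.8 |
| 0.60 | 1.5 | 5.4 vs 3.6 | 10.8 vs 7.2 |
| 0.50 | 1.8 | 5.4 vs 3.0 | 10.8 vs 6.0 |
| 0.30 | 3.0 | 5.4 vs 1.8 | 10.8 vs 3.6 |

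The article states no between-arm test of adverse events, so no false-positive rate is attached to these figures.

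**Blinding: the statements in order**

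1. Therapists are unblinded and record events from sessions that exist in one arm only.
2. Those events go to the principal investigator or a designated clinician for a judgement of relatedness to the intervention.
3. The principal investigator and clinicians are both listed as having no access to group assignment.

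Choosing the designated clinician instead of the principal investigator does not resolve the conflict as written, because clinicians are in the blinded list too.

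**The case against.** The strongest reply is that the article does not leave controls unobserved.

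- Intensified care is logged in both arms.
- All participants stay under their clinical team, and usual care includes symptom monitoring.
- Treating staff are consulted when significant symptoms emerge, and the team reviews safety monthly.
- The HDRS-17 is given by blinded assessors to both arms at T1 and T2, so worsening on the scale is measured alike.
- Serious events, such as psychiatric hospitalization, depend less on a therapist asking.
- No between-arm test of harms is stated, and extra detection would count against the program.
- An article condenses a fuller protocol, which may describe event forms for both arms.
- Learning the arm of one reported case is not the same as having access to the allocation list, and nothing makes the principal investigator an HDRS-17 rater.

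Most of this stands and sets the limits of the point. It does not remove the point. The routes shared by both arms are passive and favour events that have already reached clinical services. The HDRS-17 gives severity at two visits but no record of events between them. The article is also not merely silent: it names a method of enquiry, and that method exists in one arm only. On blinding, the wording conflict remains even if no outcome is affected.

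Three stronger readings are tempting, and the documents do not support them. A reader might infer that deterioration in controls goes unseen for 12 weeks; usual care and the logging of intensified care contradict that, and the supportable statement is that the trial does not actively seek it. A reader might infer that no harms can be compared; scale-measured worsening and serious events are much less exposed. A reader might also infer that efficacy is biased, because worsening can lead to discontinuation and may be noticed more in one arm. That path is conceivable, but the article gives nothing from which to show that it operates or how large it would be.

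**Conclusion.** The point holds in a limited form. As written, logged adverse events, mainly non-serious psychological ones, will be detected more readily in the experimental arm, and their rates should not be compared between arms. The direction follows from the design. The size does not: the 1.5- to 3-fold apparent excess is an illustration that rests wholly on assumed detection of 90% against 60% to 30%. The primary analysis is not directly at issue.

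The conflict between Adverse Events and Blinding is a matter of wording and needs no assumption. A blinded judgement of relatedness would be no fault in itself. The fault is that the source of a report can disclose the arm to someone declared blinded. This shows no bias in the HDRS-17, whose raters are blinded under a separate provision.

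The change is worth making but does not threaten the trial's main conclusion. The remaining uncertainty is whether a fuller protocol already describes an enquiry common to both arms. If it does, only the blinding conflict is left.

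**What to change.** 1. **Common enquiry.** Put the same structured adverse-event and worsening questions to both arms on the same schedule, as a self-completed REDCap form at T1 and T2. It should be completed after the HDRS-17 and not be visible to its rater, because answers may mention therapist sessions. If feasible, add the same form at identical interim weeks in both arms. Add the row to Table 1.
2. **Reporting.** Base any between-arm summary of harms on this common source, and list therapist-elicited events separately, without comparison.
3. **Relatedness.** Reconcile Adverse Events and Blinding: name who judges relatedness, state that this person may be unblinded and takes no part in outcome assessment or analysis, and amend the Blinding list to exempt that role. Serious events are reported to the principal investigator within 24 hours, so Blinding should also acknowledge that an individual report may disclose an arm.

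The cost is a protocol amendment, one form in a system already in use, a small burden on participants, and some existing staff time to review the forms. How the team responds to a worrying answer is a clinical matter for the safety section and is not proposed here.

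One limit remains: participants know their arm, so a common form equalises the opportunity to report but not necessarily the willingness.

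Timing favours an early change. Data collection began in March 2026 and 8 women were enrolled by April 2026. Counting 12 weeks from the start of March, nobody could reach T1 before late May 2026.

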### Data Management

Data will be collected, and managed using the REDCap electronic data capture system [33], hosted by the HMRI, which provides a secure and reliable platform for managing research data. Access to the data will be safeguarded by a password-protected system, with user permissions defined by individual roles and access levels assigned through unique user IDs.

Original signed consent forms will be securely stored in numerical order in locked cabinets at the study site. These documents will be retained for 5 years following the conclusion of the study, with access restricted to authorized personnel only.

### Data Analysis

#### Sample Size Calculation

A total sample size of 120 participants (60 per group) is required. This estimation was calculated based on a design with 2 groups and 3 measurement points. Assuming an effect size of *f* of 0.15, a significance level of *α* of .05, and a power of 0.90, with a correlation among repeated measures of 0.5 and assumed sphericity (*ε*=1), the minimum sample size estimated was at 96 patients. This number was increased to 120 to account for an anticipated 20% attrition rate. The sample size was determined using G*Power version 3.1.7.

#### Statistical Analysis

The statistical analysis plan was developed in collaboration with 2 biostatisticians. The analysis will be performed using SPSS Statistics (version 26; IBM Corp.).

Descriptive statistics will summarize sociodemographic and biomedical variables at baseline. Metabolomic variables will be analyzed across all time points; a complete list of the metabolomic variables analyzed in each matrix is provided in Table S3 in Multimedia Appendix 1. Continuous variables will be presented as means and SDs or medians and IQRs, depending on the distribution, while categorical variables will be reported as frequencies and percentages.

#### Outcome Analysis and Longitudinal Modeling

Primary and secondary outcomes will be analyzed using an intention-to-treat (ITT) approach, with all participants analyzed according to their original randomization group. Linear mixed-effects models (LMMs) will be used to examine changes over time and between groups for the HDRS-17, WHODAS 2.0, EQ-5D-5L, PSS, and MEDI-Q scores. These models will include fixed effects for group, time, and their interaction, with a random intercept for participants to account for within-subject correlation over time.

While change scores may be calculated for descriptive or interpretative purposes, the LMMs will serve as the primary inferential approach. In the event of a significant group × time interaction, post hoc simple effect analyses will be conducted to evaluate between-group differences at a specific time point and within-group changes from baseline, using estimated marginal means with appropriate corrections for multiple comparisons.

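### Therapists treat only the experimental arm, yet the primary model and sample size assume independent women; any therapist clustering would make the HDRS-17 standard error too small for the wider conclusions the article draws

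*Protocol article*

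**What the plan says.** Under Experimental Group, the protocol article states that "participants will receive 6 individual online sessions with a trained female psychologist". Therapists also set the order of the modules, "allowing therapists to tailor each participant’s module sequence based on individual needs and clinical relevance". The section on adherence describes the sessions as up to 6 per woman. According to Study Setting, therapists run them from the hospital's own premises. The experimental arm has a further shared element: "Participants will also have access to an online peer support group, moderated by a trained female facilitator".

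Under Control Group: "Control group participants will not receive interactive tasks or one-to-one sessions with a therapist".

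The primary analysis is written out under Outcome Analysis and Longitudinal Modeling: "These models will include fixed effects for group, time, and their interaction", "with a random intercept for participants to account for within-subject correlation over time". No other random effect is named. Under Sample Size Calculation, "A total sample size of 120 participants (60 per group) is required". That figure comes from a repeated-measures calculation with no therapist count, ICC or design effect. The limitations in the Discussion do not mention therapist effects.

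**The concern.** This is a partially nested design: women in one arm are grouped under therapists and women in the other are not. A participant random intercept absorbs the correlation between repeated scores of the same woman. It does nothing for the correlation between different women treated by the same therapist. Where that correlation is positive, the experimental arm holds less information than its number of women suggests, and the model reports too small an SE for the group-by-time effect. The test then rejects too often and the confidence interval is too narrow. The stated power is also too high.

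This matters because the article describes the trial as a confirmatory superiority trial and looks beyond the therapists employed. The abstract's conclusions and the Discussion present the program as scalable to public health systems, with therapists trained in a single workshop.

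**Working it through.** **Inputs from the article.** Effect size f = 0.15, alpha = .05, power 0.90, 2 groups, 3 time points, correlation 0.5, sphericity 1, minimum 96, 20% attrition, 120 randomized 1:1, two-tailed tests.

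**Inputs assumed, because the article does not give them.** Number of therapists k = 2 to 10, therapist ICC = 0.01 to 0.10, equal caseloads. I use 48 analysed per arm, because the stated 0.90 power belongs to 96 analysed women and not to the 120 randomized.

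**Step 1: reproduce the plan's figure.** For the group-by-time interaction, the noncentrality is lambda = f² × N × 3 / (1 − 0.5) = 0.135 N, with 2 and 2(N − 2) degrees of freedom.
- N = 94: power 0.896.
- N = 96: lambda = 12.96, power 0.902.
- 96 / (1 − 0.20) = 120.

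The stated figures reproduce exactly, with every woman treated as independent.

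**Step 2: clustering in one arm.**
- Women per therapist: m = 48 / k.
- Design effect in the experimental arm: DE = 1 + (m − 1) × ICC. In the control arm it is 1.
- Variance ratio of the group difference: VR = (DE + 1) / 2.
- SE ratio (true / planned) = √VR.
- Type I error of the nominal 5% test ≈ 2 × [1 − Φ(1.96 / SE ratio)].
- Power at N = 96: as in Step 1, with lambda = 12.96 / VR.

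Worked case, k = 4 and ICC = 0.05: m = 12; DE = 1 + 11 × 0.05 = 1.55; VR = 2.55 / 2 = 1.275; SE ratio = 1.129; type I error 0.083; lambda = 12.96 / 1.275 = 10.16; power 0.816.

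| Therapists | ICC | DE | SE ratio | Type I error | Power at 96 |
|---|---|---|---|---|---|
| 10 | 0.01 | 1.04 | 1.01 | 0.052 | 0.90 |
| 10 | 0.10 | 1.38 | 1.09 | 0.072 | 0.84 |
| 4 | 0.01 | 1.11 | 1.03 | 0.056 | 0.89 |
| 4 | 0.05 | 1.55 | 1.13 | 0.083 | 0.82 |
| 4 | 0.10 | 2.10 | 1.25 | 0.115 | 0.73 |
| 2 | 0.05 | 2.15 | 1.26 | 0.118 | 0.72 |
| 2 | 0.10 | 3.30 | 1.47 | 0.181 | 0.58 |

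The power column allows for the larger variance but not for the degrees of freedom lost when there are few therapists.

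**Step 3: check against the planned test.** The formula in Step 2 is for a single contrast, whereas the planned test has 2 degrees of freedom. I therefore simulated the random-intercept group-by-time F test with 48 per arm, adding a therapist effect at 12 and 26 weeks in the experimental arm only. With no therapist effect it rejected in 5.3% of runs. With 4 therapists and ICC 0.05 it rejected in 8.2%, with 2 therapists and ICC 0.10 in 18.3%, and with 10 therapists and ICC 0.01 in 5.1%. These agree with the table.

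**The case against.** **The size is unknown.** The article gives no therapist count, caseload or ICC, and shared caseloads are themselves an inference, from about 60 women with up to 6 sessions each (60 × 6 = 360 sessions) delivered from one hospital. With 10 therapists and ICC 0.01 the SE ratio is 1.01. This stands, and it is why the conclusion is conditional.

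**Tailoring is not therapist variation.** A reader might infer that delivery differs between therapists by design. The article does not say so: the sequence follows each woman's needs, the modules are common to all, and every therapist is trained in the program. Variation between women does not by itself create correlation within therapists. The point rests on shared therapists, not on tailoring.

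**Therapists are part of the program.** A reader might also infer that a benefit produced by good therapists is not a program effect. That does not follow, because therapist support is one of the program's components. If conclusions were confined to the therapists employed, the planned SE would be defensible. This stands too, but the article's conclusions on scalability are not so confined.

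**The analysis plan is not shown.** It may contain a therapist sensitivity analysis. But the primary model and the sample size basis are stated in the article, and what those two statements imply can be judged as they stand.

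**A partially nested primary model could be costly.** With few therapists the between-therapist variance is barely estimable. At ICC 0.05, the Satterthwaite approximation (DE + 1)² / [DE² / (k − 1) + 1 / 47] gives about 5 degrees of freedom for 3 therapists (critical t about 2.6) and about 2 for 2 therapists (critical t about 4.0). This is a good reason not to replace the primary model.

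**Conclusion.** The concern holds conditionally. The stated model and sample size treat women in the experimental arm as independent although they very likely share therapists. For any positive therapist ICC, the planned SE is too small for inference beyond those therapists. Under the assumed ranges the true SE is 1.01 to 1.47 times the planned SE, type I error is about 5% to 18%, and power runs from about 0.90 down to 0.58. A middle case of 4 therapists and ICC 0.05 gives 1.13, about 8% and about 0.82.

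A reader might go further and infer that the SE is known to be materially wrong, or that the trial must be enlarged. The documents support neither, because the answer turns on two figures they do not give. The moderated peer group is another possible source of correlation in the experimental arm only; it is not quantified here.

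**What to change.** 1. Record a therapist identifier for every experimental participant.
2. Keep the stated mixed model as primary. Pre-specify a sensitivity analysis of the HDRS-17 effect that allows for therapist clustering in the experimental arm only. With enough therapists, use a partially nested model with small-sample degrees of freedom. Otherwise, recompute the SE and interval over a stated ICC range, for example 0.01 to 0.10.
3. State under Sample Size Calculation that the 0.90 power assumes no therapist effect.

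The cost is one data field, one extra table and a less favourable stated power. The interval in the sensitivity analysis will be wider, possibly much wider if there are very few therapists. The timing is good: 8 women had been enrolled by April 2026 and analysis had not begun, so the change can be fixed in advance through the amendment process the article describes.
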